## **19. Data management**

After the evaluations, the data will be tabulated and treated statistically by a researcher experienced in data analysis. To avoid possible errors, a second researcher should check the tabulated data and replicate the analyses.

## **20. Statistical methods**

**20a.** Aiming at greater robustness and precision in data analysis, analysis of co-variance (ANCOVA) is planned, with baseline data used as co-variables, so that, strictly speaking, the effective differences between the groups in the post-intervention period are compared.

**20b.** In order to demonstrate the effects of the intervention considering only the subjects who completed the protocol, an analysis per protocol is also foreseen, even if in a secondary way.

**20c.** For the main analyses, performed on an intention-to-treat basis, imputations are anticipated for participants who do not complete interventions. In this case, data from the initial assessment (pre-intervention) will be replicated in the final assessment (post-intervention).

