#### Exclusion Criteria

- start practicing another type of physical exercise during the study period
- not being able to perform the pre-intervention assessment or the intervention exercise protocol
- emergence of lesions that do not allow the continuity of interventions
- withdraw from participating in the study

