### 11. Interventions

**11a.** Intervention 1 – Traditional Pilates: This group will perform a traditional Pilates session, which consists of stretching exercises, followed by exercises to strengthen the core (trunk flexors and extensors), lower limbs and upper limbs. The total duration of the intervention in this group should be approximately 50 minutes.

Intervention 2 – Pilates without stretching: This group will conduct a non-traditional Pilates session. This is because stretching exercises will be excluded. The muscle strengthening exercises will be the same as in the TP group, so that it is possible to discuss the influence of the inclusion/exclusion of stretching for the considered outcomes. The total duration of the intervention in this group should be approximately 35 minutes.

**11b.** a participant must discontinue the intervention when at his own request (personal reasons), or due to any health problem that makes its continuity unfeasible (eg appearance of injury).

**11c.** adherence monitoring will occur through an attendance/absence form.

**11d.** all participants will be instructed to maintain their usual routine, especially with regard to physical activity and eating habits.

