*Muscular resistance of the trunk extensors* – To assess the muscular resistance of the trunk extensors, the Sorensen test will be used. The participant must be in ventral decubitus with the lower extremity of the body attached to a stretcher, with the region of the anterior superior iliac crest demarcating the final point of support. Before starting the test, the participant will be allowed to support the upper extremity of the body, located outside the stretcher, on a chair. The test will start when the participant raises the trunk and remains without touching the chair, with arms crossed in front of the chest, and keeping the trunk parallel to the ground as long as possible. The test will be stopped when the participant is unable to sustain the position or is prompted more than 2 times to align the trunk and maintain the neutral position. This test demonstrated moderate to high test-retest reliability in healthy adults ( $ICC \geq 0.76 \leq 0.97$ ) [28].

*Flexibility* – To assess the flexibility of the posterior region of the body, the sit-and-reach test with the Wells bench will be used. The participant must sit facing the bench, with bare feet, knees extended and soles of the feet in contact with the bench. The participant should extend her arms over the surface of the bench, with her hands positioned one over the other, coinciding with the tip of her middle fingers. Anterior trunk flexion will be requested, keeping the arms extended and the hand touching the measurement scale, trying to reach the greatest possible distance in a slow movement and without jerks. For

the purpose of the final result of the test, the greatest distance achieved in the series of three attempts will be computed. This test demonstrated high test-retest reliability ( $r = 0.98$ ) [29].

*Affective valence* – Assessment of affective valence will be performed by the Feeling Scale, which ranges from +5 (very good) to -5 (very bad). Positive values represent pleasure, while negative values represent displeasure. The answers will always be collected at the end of the exercise sessions. The adapted version of this scale for the Brazilian population showed high reproducibility ( $ICC = 0.64$ ) [30].

**18b.** All randomized participants will be evaluated post-intervention considering the group to which they were initially allocated. All initially randomized participants will be analyzed post-intervention. An intention-to-treat analysis is therefore planned.

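### Section 20c triggers baseline imputation by not completing the sessions rather than by a missing post-test, so its literal wording would replace measured values in the main analysis

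*Protocol*

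**What the plan says.** Protocol Section 20a plans the comparison of post-intervention values: "analysis of co-variance (ANCOVA) is planned, with baseline data used as co-variables". Section 20c deals with the main, intention-to-treat analyses. There "imputations are anticipated for participants who do not complete interventions", and in that case "data from the initial assessment (pre-intervention) will be replicated in the final assessment (post-intervention"). No further condition is attached.

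Section 18b (Data collection methods) states: "All randomized participants will be evaluated post-intervention considering the group to which they were initially allocated". It adds: "All initially randomized participants will be analyzed post-intervention".

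Section 11b covers stopping the intervention, at the participant's own request or for a health problem. It does not say that the final assessment is then dropped. The Exclusion Criteria separately list those who "withdraw from participating in the study". For completers only, Section 20b says that "an analysis per protocol is also foreseen, even if in a secondary way".

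**The concern.** Imputation should depend on whether an outcome is missing. Section 20c makes it depend on whether the sessions were completed. The two conditions overlap but differ, and they part company for the very people whom 18b intends to keep measuring.

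A participant who stops in week 7 and attends the final assessment has a real post-test. Read literally, 20c puts the baseline value in its place and so records zero gain for someone who trained for weeks. The main analysis would then no longer compare the outcomes of the groups as randomized. With 16 per group, a few such participants are enough to move the result. Adherence could also differ between arms: sessions last about 50 minutes in one and 35 in the other (Section 11a), and participants are not blinded (Section 17a). The documents do not show that it will differ.

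**Working it through.** **1. The wording, case by case**

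| | Final assessment attended | Final assessment missed |
|---|---|---|
| Completes the sessions | Measured value used | No rule in 20c, although 18b has everyone analysed |
| Stops the sessions | Measured under 18b; on the literal wording of 20c, baseline is used instead | Baseline copied; no measured value is lost |

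Two of the four cells go wrong, and in both the cause is the trigger. No section gives an observed value precedence.

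**2. Planning figures (Section 14), used here only as a scale**

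- Means 374.3 (resistance training alone) and 337.1 (with dynamic stretching): difference 37.2 kg.
- Pooled SD = √[(37.29² + 32.07²)/2] = 34.78 kg.
- n per group = 2 × [34.78 × (1.960 + 0.842)/37.2]² = 13.72 (two-sided 0.05 assumed, power 80%). With 15% added, 13.72 × 1.15 = 15.78, so 16. The protocol's figure reproduces, and this point does not change it.

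**3. Effect of overwriting on the between-group difference**

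Let k_S and k_N be the numbers overwritten in the stretching and no-stretching arms, and g_S and g_N their mean measured gains. Overwriting sets those gains to zero, so the difference (no stretching minus stretching) moves by

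(k_S × g_S − k_N × g_N)/16.

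Assumptions not in the documents: a common training gain of 1 SD (34.78 kg), and non-completers who keep their full gain. With a true difference of 37.2 kg, g_S = 34.78 and g_N = 34.78 + 37.2 = 71.98.

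- 2 and 2: shift = −2 × 37.2/16 = −4.65; 37.2 becomes 32.55 kg. With equal numbers k the common gain cancels and the difference shrinks by k/16.
- 1 (stretching) and 4 (no stretching): shift = (34.78 − 287.92)/16 = −15.82; 37.2 becomes 21.4 kg.
- 4 and 1: shift = (139.12 − 71.98)/16 = +4.20; 37.2 becomes 41.4 kg.

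With no true difference, g_S = g_N, and 4 against 1 gives 3/16 = 0.19 of the common gain. That is 3.3, 6.5 and 9.8 kg for gains of 0.5, 1.0 and 1.5 SD.

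If non-completers keep only half their gain, each shift relative to the measured data is halved (2 and 2: −2.3 kg).

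**4. Simulation of the ANCOVA**

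16 per group, 6,000 trials per setting, pre-post correlation 0.5, 0.7 and 0.9, full gain kept; common gain 1 SD in the rows with a true difference:

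| Overwritten (stretching, no stretching) | True difference | Estimate, overwritten | Rejection rate, overwritten | Rejection rate, measured values |
|---|---|---|---|---|
| 2, 2 | 37.2 | 32.4 to 32.6 | 0.75 to 1.00 | 0.91 to 1.00 |
| 1, 4 | 37.2 | 21.3 to 21.4 | 0.29 to 0.60 | 0.92 to 1.00 |
| 4, 1 | 37.2 | 41.4 | 0.95 to 1.00 | 0.91 to 1.00 |
| 4, 1 (gain 0.5 to 1.5 SD) | 0 | 3.2 to 9.8 | 0.06 to 0.09 | about 0.05 |

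With measured values the estimates were about 37 kg and about 0 respectively, so the formula in step 3 is confirmed.

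**The case against.** The best reply is that to impute ordinarily means to fill a gap, and that 20c only anticipates imputation. On that reading non-completers are expected to lack a post-test, 18b states who is followed and analysed, and 20c says how those without data are kept in. This may well be what the authors meant. It does not settle the matter, because 20c names a different condition and no other section supplies the missing one.

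Three stronger readings are tempting, and the documents do not support them.

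- That the main analysis will certainly discard real data. This follows only from the literal wording. Those who withdraw from the study, or whose injury rules out strength and jump tests, may have no post-test to replace.
- That 18b and 20c cannot both be followed. On the missing-data reading they fit. Even literally, everyone could be assessed and then analysed with a copied value, which wastes data but is possible.
- That the bias equals the shift in one arm's mean. Three of 16 with gains of 0.5 to 1.0 SD shift that mean by 3 × 0.5/16 = 0.09 to 3 × 1.0/16 = 0.19 SD. The trial compares arms that do the same strengthening, so with equal non-completion the common gain cancels and only attenuation remains. Large distortion needs clearly unequal non-completion, and even 4 against 1 raised the type I error only to 0.06 to 0.09.

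The loss allowance of 15% is about 2 per arm (0.15 × 16 = 2.4), so the milder scenario is the one nearest to the plan's own expectation.

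**Conclusion.** The point holds as a defect of wording in the main analysis. Section 20c ties baseline imputation to non-completion. Followed literally, it replaces measured post-tests of participants who stopped the sessions but were assessed, and it leaves completers without a post-test uncovered. This is not detail left to a later analysis plan, because the protocol itself fixes both the trigger and the imputed value.

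The size cannot be derived from the documents: completion has no definition, and an unknown share of non-completers will have no post-test. The figures above are illustrations. They rest on assumed numbers of non-completers, an assumed common gain, full retention of that gain, and a planning difference taken from a leg-press test rather than from this trial's own outcomes. Under them the error runs from modest attenuation (37.2 to about 32.5 kg with 2 per arm) to bias in either direction when non-completion is unequal. Using the measured values removes it.

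**What to change.** Reword 20c along these lines: *Participants who stop or miss sessions are still invited to the final assessment. Every observed post-intervention value is used in the main intention-to-treat analysis, whatever the participant's adherence. Imputation applies only where the post-intervention value is missing, including for participants who completed the sessions.* Non-completion then serves only to define the secondary per-protocol set in 20b, and what counts as completing should be stated there before the data are analysed; the attendance form in 11c already records what is needed.

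The cost is a few sentences, entered through the amendment route in Section 25. No visit, participant or measurement is added, since 18b already plans to assess everyone. Whether copying baseline is a good method for values that are truly missing is a separate question, which this change leaves open.

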## **METHODS: MONITORING**

### **21. Data monitoring**

**21a.** For the present study, a data monitoring committee is not foreseen.

**21b.** No interim analysis is foreseen.

### **22. Harms**

In all sessions, participants will be asked about the possible occurrence of adverse events.

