## **30. Ancillary and post-trial care**

According to the project approved by the Ethics Committee, if any participant suffers damage as a result of the study (eg injury), he will receive free treatment until he improves.

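### Section 22 sets adverse-event questions at exercise sessions and at no other time, so harms in people who stop attending, or arising after the last session, may not be systematically asked about or recorded.

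*Protocol*

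**What the plan says.** Section 22 (Harms) is one sentence: "In all sessions, participants will be asked about the possible occurrence of adverse events". It is the only statement in the protocol on how adverse events are collected.

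Other sections bear on who is present to be asked:

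- Section 10, under the exclusion criteria, lists "emergence of lesions that do not allow the continuity of interventions" and "withdraw from participating in the study". Both can arise after randomisation.
- Section 11b names injury as an example of a health problem that ends the intervention.
- Section 11c says "adherence monitoring will occur through an attendance/absence form". It does not say that the reason for an absence is noted.
- Section 13 places the final evaluations in the week after the eight weeks of intervention.
- Section 18b says "All randomized participants will be evaluated post-intervention considering the group to which they were initially allocated". No harms question is attached to that evaluation.
- Section 20c says "imputations are anticipated for participants who do not complete interventions", by carrying the baseline value forward.
- Section 30 says "if any participant suffers damage as a result of the study (eg injury), he will receive free treatment until he improves".

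**The concern.** The harms question depends on turning up to exercise. People who stop turning up are not a random subset, because the protocol itself gives injury as a reason for stopping. The rule is therefore thinnest where harm is most likely to have occurred.

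A second gap does not depend on drop-out. A complaint that appears after the last session, or that comes from the final tests, has no later session at which it would be asked about. This applies to every participant.

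At stake is whether the trial's description of harms is complete and gathered in the same way for everyone. When participants are asked is a data-collection rule: an answer that was never sought cannot be recovered at analysis.

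**Working it through.** The protocol states no adverse-event rate, so there is no figure to reproduce. The check is a reading of the sections together, followed by arithmetic for scale only.

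**Reading**

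1. *During the programme, while attending.* Section 12 implies 24 sessions (3 per week for 8 weeks). Section 22 covers all of them, so questioning is frequent.
2. *After a participant stops.* There are no more sessions, so section 22 no longer reaches that person. Sections 10, 11b and 11c provide for exclusion, discontinuation and an attendance record, but none provides a harms question.
3. *At the final assessment.* Section 18b plans it for everyone randomised, but no harms question is attached. Section 20c anticipates that some non-completers will need imputed values, so the visit cannot be assumed to happen for everyone who stops.
4. *After the last session and in the final tests.* Section 18a describes repetitions to the limit against elastic bands, repeated vertical jumps, maximal grip, one minute of sit-ups and a sustained trunk hold. No session follows.
5. *Other routes to knowledge.* Section 11b implies that the team learns why someone discontinues, and section 30 offers treatment for injury caused by the study. Neither section says that the event is recorded as an adverse event.

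**Scale**

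Inputs: 16 per group, 32 in total, with a 15% allowance for loss (section 14). The 15% is a sample-size allowance and is used here only as an assumed stopping rate.

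- One event in a group: 1/16 = 6.25%.
- Assumed number stopping: 16 × 0.15 = 2.4 per group; 32 × 0.15 = 4.8 in total, leaving 27.2 attending.
- If no events are recorded, the one-sided 95% upper bound is 1 − 0.05^(1/n). For n = 16 it is 17.1%; for n = 14, 19.3%; for n = 13, 20.6%. The last two treat people who stopped as if they had never been asked, although they were asked at each session they attended, so they are outer limits.

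**Illustration under assumed rates (none is in the protocol)**

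Suppose 5% to 20% of attenders and 10% to 50% of those who stop have an event, and every event among those who stop goes unrecorded.

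- Events missed: 4.8 × 0.10 = 0.48, up to 4.8 × 0.50 = 2.4.
- Smallest share of affected participants missed: 0.48 / (0.48 + 27.2 × 0.20) = 0.48 / 5.92 = 8%.
- Largest share missed: 2.4 / (2.4 + 27.2 × 0.05) = 2.4 / 3.76 = 64%.

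The width of that range shows that the documents do not determine the size of the gap.

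**The case against.** The best defence is that section 22 sets a minimum. It says participants are asked at every session; it does not say that harms are collected in no other way, and that exclusivity is inferred from silence elsewhere. The defence is strongest for injuries that end participation. The criteria in sections 10 and 11b can be applied only if the team knows of the injury, section 30 gives the injured person a reason to come forward, and an event during a supervised session or a final test would probably be seen by staff. Section 18b also plans a later contact with everyone randomised. Nor does any section say that the events of excluded participants are discarded.

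Most of this stands, and it rules out saying that injured people who stop are missed altogether. What it does not supply is a recording rule. Learning of an event informally is not the same as asking everyone the same question and writing down the answer.

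A reader might go further and infer that harms are in fact under-counted, or that a comparison of the two groups would be biased toward safety or toward one arm. The documents do not support either inference. Adverse events are not among the objectives (section 7) or outcomes (section 12), section 20 plans no between-group comparison of harms, and no loss or injury rate by group is given.

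**Conclusion.** The point holds as a gap in the stated collection rule, and as a minor one. Section 22 provides for questions at sessions and at no other time, so harms in people who stop attending, and events after the last session or from the final tests, may not be systematically asked about or recorded. Some injuries would become known anyway.

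The size and direction of any under-count cannot be computed from the documents. What can be said is that one unrecorded event is 6.25 percentage points in a group of 16. A reader might take the 2 to 3 people per group who could stop and infer that a group with no recorded events has a true rate of 2/16 = 12.5% to 3/16 = 18.8%. That requires every one of them to have had an event that nobody recorded, and nothing in the protocol supports it.

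**What to change.** In section 22:

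- Ask the same adverse-event question at the post-intervention assessment that section 18b already plans for all randomised participants, with wording that covers the period since the last session and the tests themselves.
- Ask it once more, by brief contact, when a participant discontinues.
- Record the reason for each discontinuation, so that an injury behind it is captured as an adverse event.
- Report events by randomised group for all randomised participants, including those who later meet an exclusion criterion.

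The cost is one extra question at an existing visit and a short contact for the few who stop. The design, the sample size and the efficacy analysis do not change.

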### **23. Auditing**

No audit is planned for this study.

## **ETHICS AND DISSEMINATION**

### **24. Research ethics approval**

The ethical norms established in the Declaration of Helsinki (1975, revised in 1983) were followed, and the study was approved by the Human Research Ethics Committee of the Universidade Estadual do Norte do Paraná, Brazil, before its beginning under the opinion number 5.548.126.

### **25. Protocol amendments**

Any need to change the study protocol should be done via [clinicaltrials.gov](https://clinicaltrials.gov), which maintains an online record of changes that can be accessed by anyone.

### **26. Consent or assent**

**26a.** The principal investigator will obtain informed consent from each participant. For this, he should explain in clear language all aspects of the study, such as: evaluation measures, intervention procedures, risks and benefits. In addition, a Consent Term approved by the Ethics Committee that approved the study must be read by the participant, who must sign the document if he/she wishes to participate in the study.

**26b.** If it is necessary to use the image of a person demonstrating the exercises of the intervention protocol, an informed consent will also be required specifically for this purpose.

### **27. Confidentiality**

No personal data of participants will be kept in the study's digital databases. From the randomization process, the participants will be numbered and for purposes of data tabulation and analysis only these numbers will be used.

### **28. Declaration of interests**

The study researchers declare that there are no conflicts of interest to declare for this work.

## **29. Access to data**

The final data of the study were under the custody of the main researcher, who can provide access upon a formal request.

## **30. Ancillary and post-trial care**

According to the project approved by the Ethics Committee, if any participant suffers damage as a result of the study (eg injury), he will receive free treatment until he improves.

## **31. Dissemination policy**

**31a.** The results of the study should be published in a scientific journal (preferably with open access), in order to give a wide coverage to the findings.

**31b.** Eligibility for authorship will be defined according to the recommendations of the International Committee of Medical Journal Editors (ICMJE).

**31c.** Data referring to the protocol can be accessed via [clinicaltrials.gov](https://clinicaltrials.gov), while the spreadsheet containing data from pre- and post-intervention evaluations, as well as the statistical code, can be requested directly from the main researcher.

